### Sample size and power calculations

The total number of participants with data in line with the primary study objectives is expected to be n=450. This assumes 4 years of data from 90% of 500 enrolled participants and is based on attrition rates in previous National Health and Medical Research Council (NHMRC) funded cohorts run by the CI team. If the HD prevalence in approximately 70% of the total cohort is assumed, the AusCP MSK study will have 90% statistical power (α=0.05) to detect absolute differences between binary risk factor categories exceeding 12%. This corresponds to detecting relative risks (RRs) falling below 0.80 or surpassing 1.24. Even when risk factors are unbalanced in a 4:1 ratio, we will be able to identify RRs of <0.74 or >1.35. For scoliosis incidence, if an overall cumulative incidence of 25% is assumed, the study will be able to detect absolute between-group differences of >11%. Note that this is an underestimate of power due to the repeated annual measurements for each child.

The bone quality cohort (C) will recruit 30 children with CP, detecting between-group differences >1.25 SD with 90% power, which are smaller differences than observed when comparing children with mild Osteogenesis Imperfecta compared with TDC.^131^

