#### Statistical analysis

Data will be stored on the research data manager hosted by lead university (The University of Queensland). To identify relationships between early biomarkers (aim 1), early brain structure (aim 2) and clinical characteristics and bone quality (aim 4) with musculoskeletal complications, we will construct multivariable regression models informed by the directed acyclic graph displayed in figure 2. The association between risk factors and primary outcomes measured on the interval scale (ie, MP%) will be investigated using mixed-effects linear regression models with child included as a random effect to account for repeated measures. Risk factor and time will be included as fixed effects, with an interaction term. Potential confounding variables will be included. For binary outcomes, mixed effects logistic regression models will be constructed and mixed effects Poisson models used for count outcomes.

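### The power section calls its figures an underestimate because of the annual repeats; this is unsupported and not generally true, and on the usual assumptions the figures are already optimistic

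*Protocol article*

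**What the plan says.** Under Sample size and power calculations, the protocol article sets the analysable number: "The total number of participants with data in line with the primary study objectives is expected to be n=450". Its basis follows: "This assumes 4 years of data from 90% of 500 enrolled participants". For hip displacement the premise is "If the HD prevalence in approximately 70% of the total cohort is assumed", and the claim is "90% statistical power (α=0.05) to detect absolute differences between binary risk factor categories exceeding 12" per cent. The text adds "This corresponds to detecting relative risks (RRs) falling below 0.80 or surpassing 1.24". For scoliosis it assumes an overall cumulative incidence of 25% and gives a detectable difference of 11 points. Directly after that comes "Note that this is an underestimate of power due to the repeated annual measurements for each child".

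Under Statistical analysis, interval-scale outcomes such as migration percentage get a linear mixed model with a random effect for child: "Risk factor and time will be included as fixed effects, with an interaction term". The next sentences read "Potential confounding variables will be included. For binary outcomes, mixed effects logistic regression models will be constructed". The interaction is not restated for binary outcomes, and neither the main effect nor the interaction is named as the decisive term.

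**The concern.** The assurance turns the stated differences into a floor: whatever the mixed models do, power is said to be at least this good. Nothing in the calculation supports that. It compares two risk groups on one status per child, whereas the planned models use up to four visits, a time term and confounders. Those are different tests with different power.

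The primary objective includes the rate of progression, so readers will want to know what a null biomarker result means. If they take 90% power at 12 or 11 points as a lower bound, they will give such a result more weight than the design can carry.

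**Working it through.** **1. The plan's own figures.** Inputs from the sample-size section: N = 450, overall rates 70% and 25%, differences d of 12 and 11 points, α = 0.05, power 90%. Assumed, because not stated: 225 v 225 and a two-sided test. No formula is named, so I used the standard comparison of two proportions:

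z = (d − 1.96·s0)/s1, with s0 = √[2p̄(1−p̄)/225], s1 = √[(p1(1−p1) + p2(1−p2))/225], power = Φ(z).

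- Hip, 76% v 64%: s0 = 0.04320, s1 = 0.04283, z = (0.12 − 0.08468)/0.04283 = 0.825, power 79.5%.
- Scoliosis, 30.5% v 19.5%: s0 = 0.04082, s1 = 0.04049, z = (0.11 − 0.08002)/0.04049 = 0.740, power 77.0%.
- Solving for 90% power gives 13.9 points (hip) and 13.2 points (scoliosis). The stated differences fit about 80% power, which needs 12.1 and 11.4 points.

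Other readings, also 1:1:

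- Two-sided with N = 500: 83.6% and 81.3%.
- Two-sided, N = 450, with 70% as the lower group's rate and 25% as the higher group's: 84.9% and 84.0%.
- The same reading with a one-sided test: 91.1% and 90.5%. This reaches 90%, but the text applies its rates to the whole cohort and gives relative risks in both directions, which fits a two-sided test.

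The quoted relative risks do not match 12 points either. Around an overall 70%, 12 points is 0.84 or 1.19, while 0.80 and 1.24 correspond to 15 to 16 points.

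**2. Cumulative incidence.** By T4 each child either has or has not crossed the threshold. With complete data, the T4 contrast between two groups of 225 has the precision in step 1 however many earlier visits there were.

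**3. Repeats in a linear random-intercept model** (four equally spaced visits, within-child correlation ρ, no random slopes; ρ is not in the documents).

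- Difference constant over visits, main effect tested: variance is multiplied by (1 + 3ρ)/4, which is at most 1. Repeats help or are neutral.
- Difference growing from zero, interaction tested: the slope difference is d/3 per visit and the squared centred visit times sum to 5. Relative to the single-visit test, the statistic is therefore (√5/3)/√(1−ρ) = 0.745/√(1−ρ). It is larger only if ρ exceeds 0.44.
- Difference growing from half to full size: the factor halves, and break-even is at ρ = 0.86.

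**4. Repeats with a binary outcome** (simulation, 225 v 225, four visits, at least 1,000 runs per row). Threshold status is irreversible, and the analysis is a marginal logistic model with robust variance, standing in for the mixed logistic model. T1 prevalences of 10% (scoliosis) and 40% (hip) are assumptions. Differences at T4 were set at 13 and 14 points, where the single-visit test has about 90% power.

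| Outcome and pattern | T4 only | Main effect, all visits | Interaction |
|---|---|---|---|
| Scoliosis, proportional to prevalence | 90% | 82% | 8% |
| Scoliosis, no difference at T1 | 89% | 51% | 78% |
| Hip, proportional to prevalence | 91% | 79% | 38% |
| Hip, no difference at T1 | 91% | 39% | 93% |

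Repeat runs moved these by up to about 3 points. With a constant odds ratio the hip main effect rose to 98%, while scoliosis stayed at 86% to 87% against 89%.

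**5. Confounders.** Using n(1−R²) as an approximation, where R² is the share of the risk factor explained by confounders (assumed), power = Φ(3.24√(1−R²) − 1.96). That is 83% at R² = 0.2 and 71% at R² = 0.4.

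**The case against.** The best defence is that repeats do help in recognisable cases: a difference constant over visits tested as a main effect, or groups that start equal and diverge with high within-child correlation. Steps 3 and 4 show both. The interval-scale analysis of migration percentage may also be more sensitive than any threshold comparison, though that gain comes from the scale and not from the repeats. All of this stands, and it is why the sentence is better called unsupported and not generally true than simply wrong.

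A reader might go further and infer that the planned risk-factor-by-time test usually has much less power than stated, so that the study is underpowered for progression. The documents do not support that:

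- The interaction is written only for interval-scale outcomes, while the power figures concern binary ones.
- No term is named as decisive.
- T1 prevalence, trajectory, correlation and irreversible status are assumptions. Hip displacement is given as a prevalence and can be treated surgically, so the count-once argument applies firmly to scoliosis only.
- Under a constant odds ratio there is no interaction on the logit scale, so rejection rates of 4% to 6% are test size, not lost power. The proportional scoliosis case is close to this: its odds ratio moves only from 1.80 to 2.03.

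The confounder calculation is generic and does not bear on the sentence about repeats. It shows only that adjusted effects lie outside the stated figures. Finally, a condensed article may leave a simulation of the planned model to the full protocol or the SAP. That is fair, but this sentence is a positive claim made in the article itself.

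**Conclusion.** The concern holds as a point about a stated power property that the design does not generally have. For the scoliosis cumulative incidence, repeats add nothing to the comparison that was powered. For a repeated-measures model, the direction depends on the term tested, the correlation and the trajectory. In the scenarios of step 4's table, interaction power ran from about 8% to 93% against about 90% at a single visit. That range illustrates dependence on assumptions and is not an estimate of this study's power.

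The claim also rests on figures that are not conservative to begin with. With equal groups, two-sided 0.05 and the rates taken as overall rates, power at the stated differences is 79.5% and 77.0%, not 90%. This part needs no assumption about time course.

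**What to change.** In the sample-size section:

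- Delete the sentence claiming an underestimate.
- Say that the figures are for an unadjusted, single-time comparison of two risk groups, and state the group split and sidedness.
- Correct them: about 14 points (hip) and 13 points (scoliosis) at 90% power, or about 80% and 77% power at 12 and 11 points. Recompute the relative risks to match.
- Name the final-visit contrast as the powered comparison. Add that power for the risk-factor-by-time term and for confounder-adjusted effects is not covered by these figures and may be lower.

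This is a wording change plus a short recalculation. Enrolment does not change. The cost is that the stated power looks less favourable.

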#### Statistical analysis

Data will be stored on the research data manager hosted by lead university (The University of Queensland). To identify relationships between early biomarkers (aim 1), early brain structure (aim 2) and clinical characteristics and bone quality (aim 4) with musculoskeletal complications, we will construct multivariable regression models informed by the directed acyclic graph displayed in figure 2. The association between risk factors and primary outcomes measured on the interval scale (ie, MP%) will be investigated using mixed-effects linear regression models with child included as a random effect to account for repeated measures. Risk factor and time will be included as fixed effects, with an interaction term. Potential confounding variables will be included. For binary outcomes, mixed effects logistic regression models will be constructed and mixed effects Poisson models used for count outcomes.

**Figure 2 F2:**
[figure not shown]
Directed acyclic graph model of musculoskeletal complications in children with cerebral palsy. GMFM, Gross Motor Function Measure; HPA, habitual physical activity; MP, migration percentage; PEDI-CAT, Pediatric Evaluation of Disability Inventory, Computer Adapted Test; SB, sedentary behaviour.

When constructing predictive models, important variables will be examined individually first before a final multivariable model is selected using Bayesian information criteria. Model calibration will be tested graphically, and internal calibration will use bootstrap resampling. Missing data will be treated as case-by-case basis depending on the observed pattern of missingness. For example, if data are ‘missing at random’, we will use multiple imputation methods and if data are ‘not missing at random’, we will use a pattern-mixture model. Adjustments for multiple comparisons will be made for each separate suite of analyses as appropriate, bearing in mind the type I and type II error rates for each suite.

In addition to the primary statistical analysis, a cost–consequence analysis will be performed to attain a better understanding of the value and costs of a national approach to better decision-making regarding hip, spine and bone fragility complications in CP. The cost–consequence analysis will capture the direct costs of medical care and direct non-medical costs from the HRU parent-reported questionnaire. The cost-consequence analysis will report costs and outcomes in a simple and disaggregated format to help policymakers better understand the effects of prevention programmes for musculoskeletal problems across costs and outcomes. The analysis will be performed in a 4-year time horizon with a 3% discount rate to account for time preference.

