**Trial registration number:**

Australian New Zealand Clinical Trials Registry number: ACTRN12622000788774p

STRENGTHS AND LIMITATIONS OF THIS STUDYThe study employs a prospective cohort design, allowing for the longitudinal assessment of musculoskeletal complications in children with moderate to severe cerebral palsy (CP).The study leverages multisource data linkage and imaging-based assessments across Australia and New Zealand enhancing population representativeness and generalisability.Possible risk of participant dropout and incomplete data across the study.Findings will be limited to children with moderate to severe CP (Gross Motor Function Classification System III–V) and results may not be generalisable to those with milder motor impairments.

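### The choice between multiple imputation and a pattern-mixture model is to be read off the observed missingness, which cannot tell MAR from MNAR

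*Protocol article*

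**What the plan says.** The relevant text is in the protocol article, Statistical analysis, in the paragraph after Figure 2. The governing sentence is "Missing data will be treated as case-by-case basis depending on the observed pattern of missingness". The example that follows has two branches. The first, for MAR, reads "if data are ‘missing at random’, we will use multiple imputation methods". For the opposite case, MNAR, the method named is different: "we will use a pattern-mixture model".

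Three other places bear on the point:

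- **Models.** The opening paragraph of Statistical analysis names the models in advance. Interval-scale outcomes get "mixed-effects linear regression models with child included as a random effect to account for repeated measures", with risk factor, time and their interaction as fixed effects. Binary outcomes get mixed-effects logistic models and counts get mixed-effects Poisson models.
- **Expected loss.** Sample size and power calculations states: "The total number of participants with data in line with the primary study objectives is expected to be n=450". The basis is given as: "This assumes 4 years of data from 90% of 500 enrolled participants".
- **Acknowledged limitation.** The strengths and limitations box lists "Possible risk of participant dropout and incomplete data across the study". This acknowledges the risk and is not a second instance of the problem.

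**The concern.** The text sets up a chain: the pattern of missingness shows the mechanism, and the mechanism selects the method. The first link fails. MAR means that, given what was recorded, the chance of a value being missing does not depend on the missing value itself. MNAR means that it does. The distinguishing information lies in the values that are absent, so no tabulation of who is missing, and when, can settle it.

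Three consequences follow:

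- The rule gives the analyst no usable instruction.
- The method is settled by judgement after the data are available, and the judgement may differ between hip, spine and bone outcomes.
- The two methods are presented as alternatives. If MAR is declared for an outcome, nothing in the rule calls for a check on how far the result depends on that assumption.

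**Working it through.** **1. The plan's own figure.** 500 × 0.90 = 450, so 50 children are expected to fall short of the full four years of data. This reproduces the stated 450 exactly.

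**2. What the observed data fix.** With 10% missing in a group, the full-group risk is

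full-group risk = 0.90 × (risk among observed) + 0.10 × (risk among missing).

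The data supply the weights and the first risk. Nothing observed supplies the second.

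**3. Illustration with assumed values.** Take two equal risk-factor groups, A and B, with 10% missing in each. Observed hip displacement is 76% in A and 64% in B: overall 70%, difference 12 points, matching the prevalence and detectable difference in the sample-size section. Suppose group is the only thing known about the missing children. Only the last term is varied.

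| Risk among missing, A / B | Full-group risk A | Full-group risk B | Difference |
|---|---|---|---|
| 76% / 64% (same as observed: MAR given group) | 76.0% | 64.0% | 12.0 points |
| 50% / 90% | 0.684 + 0.050 = 73.4% | 0.576 + 0.090 = 66.6% | 6.8 points |
| 90% / 50% | 0.684 + 0.090 = 77.4% | 0.576 + 0.050 = 62.6% | 14.8 points |
| 0% / 100% (extreme) | 68.4% | 67.6% | 0.8 points |
| 100% / 0% (extreme) | 78.4% | 57.6% | 20.8 points |

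All five rows have the same observed data and the same missingness pattern. The first is MAR and the others are MNAR. A rule that looks only at the pattern must treat them alike, so it cannot pick the right branch.

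The table shows non-identifiability and nothing more. It does not forecast bias in this study, where earlier visits on most lost children would narrow the plausible range.

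**4. An example from the article's own design.** Under Primary outcomes, DXA is done at T1 and T3, and at T4 only where a Z-score below −1.5 at any site is reported at T3. Absent T4 scans will therefore track bone density closely, and by pattern alone might be labelled MNAR. Yet this planned part depends on recorded T3 values, so it is MAR once the T3 values at all sites are in the model. Conversely, loss that depends on an unrecorded deterioration can leave an unremarkable pattern. Appearance misleads in both directions.

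**The case against.** The strongest reply has four parts.

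**The models are already fixed.** A reader might infer that the whole primary analysis would be chosen outcome by outcome after seeing the data. The article does not support that: the mixed models are named in advance. If fitted by likelihood (usual, though not stated), they use all available visits and are valid under MAR for missing outcomes when correctly specified. This stands. Only the handling of missing data is open.

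**The two branches are offered as an example, in a condensed article.** The paragraph also opens with predictive modelling, so its reach over the association models is not fully clear. Imputation variables and shift values are ordinary content for a statistical analysis plan, and their absence is no criticism. But the governing sentence, without the example, still ties the method to the observed pattern. That is an unsound rule on the page, not an omitted detail.

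**The size.** With 70% observed and 10% missing, a reader might quote the range for the full cohort, 0.9 × 0.70 = 63% to 63% + 10% = 73%, as the damage done by the rule. It is not. Those are worst-case bounds that hold under any missing-data method, including the one recommended below. More dramatic figures, such as putting all 50 losses in one group, rest on a pattern nothing in the article suggests.

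**The motive and the mechanism.** A reader might also infer that losses will be related to severity, or that the method would be chosen to suit the results. The article gives no reasons for attrition. Missingness can be examined without fitting risk-factor associations, and the Ethics and dissemination section commits to reporting deviations. Both inferences are assumptions. Nor does a pattern-mixture model necessarily need an assumed shift: it needs some untestable identifying assumption, of which a shift is one kind.

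**Conclusion.** The concern holds, confined to missing-data handling. The stated rule asks the observed pattern to distinguish MAR from MNAR, which it cannot do. What remains is a post-hoc judgement, possibly inconsistent across outcomes, with no sensitivity analysis required when MAR is declared.

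The conclusion rests on the definitions of the two mechanisms and on the wording of the governing sentence, not on any assumed attrition pattern. No numerical size is attached: the article plans for 10% loss, and the table above shows only, under assumed values, that identical observed data fit different full-cohort differences. The 450 and the choice of regression models are untouched. The correction should be made, but it does not put the study design in question.

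**What to change.** Delete the case-by-case rule and replace it with two commitments covering every primary outcome:

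1. **Primary analysis under MAR.** Use the mixed models already named, fitted by likelihood to all available visits, with multiple imputation where covariates are missing. For bone density, carry the T3 values at all sites, since they determine who is scanned at T4.
2. **Sensitivity analysis whatever pattern is observed.** Run a pattern-mixture analysis with identifying assumptions specified in advance, for example a range of delta shifts, and report how far the conclusions depend on them. This examines the dependence on MAR; it does not test MAR.

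The cost is two or three sentences and a little more analysis work. Data collection and sample size do not change. The study is due to finish on 29 February 2028, and the wording can be corrected before the final data are seen.

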## Ethics and **dissemination**

The AusCP MSK Health Network has been approved by the Children’s Health Queensland Hospital and Health Service Human Research Ethics Committee (HREC/22/QCHQ87118), The University of Queensland Human Research Ethics Committee (2022/ HE001516) and the New Zealand Health and Disability Ethics Committee (2025/FULL/21456). The trial is also registered on the Australian New Zealand Clinical Trials Registry (ANZCTR, ACTRN12622000782730p). The trial registration will be amended to reflect any protocol updates, and deviations from the protocol will be reported in the primary results manuscript. Study outcomes will be disseminated via the ANZCTR website, conference presentations and abstracts, peer-reviewed scientific journals, organisation/institution media releases and newsletters and directly to research participants in an appropriate and accessible format.

### Patient and public Involvement

An AusCP MSK consumer group, consisting of parents/families/caregivers with lived experience, has been established to provide ongoing guidance and input throughout the research process. Consumer representatives will be involved at all research stages, including study design, creation of parent/participant information and consent materials (see onlinesupplemental files 1^3^), selection of assessment materials and procedures, study implementation and dissemination of results. Ongoing broader consumer engagement will continue via the consumer network (Aus-CP-CTN CRE). The AusCP MSK consumer representatives will be financially compensated for their time and expertise. Consumer representatives will nominate their preferred method of payment (either direct credit into their account or gift card). The rate of reimbursement will be equivalent to Health Consumer Queensland remuneration rates, adjusted for annual inflation increases (1.5%). Consumer council meetings will be held no less than two times yearly, and one consumer representative will be invited to sit on the trial management committee.
